## Measures

### Clinical data collection

Patient-level clinical practice data relating to the CRC and LS referral pathway will be extracted from relevant surgical, pathology, and FCC databases by the Implementation Leads (see Additional file 2 for variables). Patient data will be collected throughout the implementation of the intervention, and outcome data will be collected for up to 9 months after the end of the intervention strategies. Patients will be eligible for inclusion if they undergo CRC resection at participating hospital networks within the time periods for data collection and are aged over 18 years at the time of resection. Given the short duration of the trial and minimal risk of harm, a formal data monitoring committee will not be required. An ethics-committee-approved data management plan has been presented to research governance officers and will be refined for each participating hospital network to ensure compliance with site-specific protocols.

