### Outcomes

#### Pre-implementation outcomes

CRC surgery, pathology, and familial cancer clinic (FCC) clinical data will be retrospectively collected across all hospital networks for patients admitted during a 24-month period prior to study commencement, to demonstrate LS referral pathway clinical practice. The data will be cross-referenced with LS referral maps to be constructed for each hospital network. The proportion of patients who transition to each step, in adherence to the pathway map will be calculated, leading to the identification of bottlenecks. The referral maps and bottlenecks will be compared across hospital networks, with particular attention to potential differences in processes between geographical regions. A validated TDF-based questionnaire (Influences on Patient Safety Behaviours Questionnaire) [37] will be used to quantitatively evaluate psychosocial barriers to risk-appropriate completion of the LS referral pathway. Qualitative focus group data will be used to understand key barriers in context.

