#### Post-implementation outcomes

The primary post-implementation quantitative outcome will be the change in the proportion of patients with risk-appropriate completion of the site-specific LS tumour testing and referral pathway within 2 months of CRC resection. Secondary outcomes will be (1) proportion of high risk-patients who were referred to the FCCs (sensitivity of referral), (2) proportion of referred patients who attended FCC and (3) proportion of patients with missing testing and referral data.

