### Allocation and concealment

Block randomisation for this study was carried out at the level of the hospital networks. Each hospital network (and associated pathology laboratory and FCC) was allocated to the theory arm or non-theory arm by a member of the research team not involved in recruitment of hospital networks, using a random computer-generated sequence, with stratification by state. The research team will be aware of the trial arm allocation to train the Implementation Leads; however, the allocation will be concealed from the Implementation Leads, and the individual participants they recruit [Implementation Team members (see Phase 2) and LS patient pathway stakeholders]. Following randomised allocation, Implementation Leads were trained in one of two structured implementation approaches: either a theory-based approach or a non-theory based approach. Allocation has been concealed from the Chief Investigators. To prevent selection bias, all hospital networks were recruited prior to randomisation, and all adult patients undergoing a CRC resection at each hospital network within the study timeframe will be included in the study. Currently, there are no anticipated circumstances when unblinding would be considered permissible. Given the inability to fully control interactions between individuals at different networks involved in the trial, we accept that masking of Implementation Leads and individual participants may be compromised. Plans to investigate the success of masking amongst Implementation Leads are being incorporated into the process evaluation.

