#### Phase 6 - support staff to implement interventions

Intervention strategies generated in phase 5 will be implemented using general implementation science principles (i.e. the need for management support and commitment among target group members, use of boundary spanners, flexibility driven by local context, incorporation into established structures) [16]. With a template provided by the research team, Implementation Leads will create a report that will outline findings from phase 1–5, the intervention package and a plan for implementation. This will be submitted to senior management from departments affected by any proposed intervention strategies (e.g. CRC surgery, pathology and FCCs), and may require revision based on management feedback. Once management approves the proposed implementation plan, intervention strategies will then be presented to relevant forums (e.g. MDT meetings, pathology team meetings) to gain feedback that will allow the development of a broader structure to disseminate findings. The Implementation Lead will then work collaboratively with the Implementation Team to implement the intervention package over a 6-month period.

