### Trial status

This study commenced in July 2017. Hospital networks have been approached to participate, have been randomised and are engaged in the governance process. Formal recruitment of hospital networks will be complete when research governance applications are approved. Recruitment of individual participants for the research activities described in phases 1–7 has not commenced, and data collection has not commenced.

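### No last resection date ahead of the end of outcome collection, and no time window for referral or clinic attendance: the pre/post contrasts are biased towards no improvement

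*Protocol article*

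**What the plan says.** All references are to the protocol article.

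- **Who is counted.** Clinical data collection: "Patients will be eligible for inclusion if they undergo CRC resection at participating hospital networks within the time periods for data collection". Allocation and concealment adds that "all adult patients undergoing a CRC resection at each hospital network within the study timeframe will be included in the study". Neither section sets a last resection date earlier than the end of collection.
- **When collection ends.** Clinical data collection: "outcome data will be collected for up to 9 months after the end of the intervention strategies". The strategies themselves are delivered earlier, when the team is to "implement the intervention package over a 6-month period" (Phase 6).
- **Primary outcome.** Post-implementation outcomes defines it as the change in the proportion with "risk-appropriate completion of the site-specific LS tumour testing and referral pathway within 2 months of CRC resection".
- **Secondary outcomes.** The same section lists referral of high-risk patients to the familial cancer clinic (FCC), FCC attendance among those referred, and the proportion with missing data. None has a time limit.
- **Missing data.** Assessing clinical practice change scores absent testing or referral information as the test not done or the referral not completed.
- **Baseline.** Pre-implementation outcomes collects data retrospectively "for patients admitted during a 24-month period prior to study commencement". Trial status says "This study commenced in July 2017" and that data collection had still not begun when the article was written.

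**The concern.** A patient resected in the last 2 months of outcome collection cannot be observed for the 2 months that the primary outcome requires. At extraction, a step not yet taken looks the same as a step never taken, and the missing-data rule scores both as failures. Baseline patients are identified retrospectively, long after their 2 months have passed. The shortfall therefore falls on the post period only.

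For high-risk referral and FCC attendance the difference is larger in kind. With no window, every patient is followed until extraction, so baseline patients have more time to be referred and seen than post patients.

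The planned exposure is pre or post status at the date of resection, and the primary outcome is a change in proportion. The bias thus falls directly on the stated contrast, and a real improvement could be understated or missed.

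**Working it through.** The article gives no sample size, power or event figure, so there is no figure of its own to reproduce.

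**Inputs from the article**
- Primary window: 2 months.
- Post period T: 9 months after the strategies end, or 6 + 9 = 15 months if roll-out counts as post.
- Volume: 8 networks at roughly 100–250 resections each per year (Study site recruitment).

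**Assumptions not in the article**
- Resections are spread evenly over T.
- Mean time m from resection to completion, among those who complete in time, lies between 0.5 and 2 months.
- Attendance waits are exponential.

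**1. Share of post patients without a full window = 2/T**
- T = 9: 2/9 = 22.2%.
- T = 15: 2/15 = 13.3%.
- In patients: 8 × 100/12 × 2 = 133 to 8 × 250/12 × 2 = 333. The post totals are 600–1,500 (T = 9) or 1,000–2,500 (T = 15).

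**2. Effect on the primary proportion.** A completion is lost when its time from resection exceeds the time left before collection ends, so observed/true = 1 − m/T.
- m = 0.5: 0.944 (T = 9), 0.967 (T = 15).
- m = 1: 1 − 1/9 = 0.889; 1 − 1/15 = 0.933.
- m = 2: 0.778; 0.867.

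With m = 1, a true ratio of 1.00 appears as 0.89 or 0.93, and a true 1.20 appears as 1.20 × 0.889 = 1.07 or 1.20 × 0.933 = 1.12. For a given m these are the largest possible distortions: not referring a low-risk patient is risk-appropriate, and truncation does not remove that success.

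The loss sits wholly in the last 2 months. With m = 1, the final 3-month interval keeps 1 − 1/3 = 0.67 of its completions, so the candidate covariate for time since implementation could show this as a waning effect.

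**3. Between arms.** Equal post lengths give the same factor in both arms, and it cancels. If one arm had 9 months and the other 6, the ratio of factors would be (1 − m/9)/(1 − m/6) = 1.03, 1.07 and 1.17 for m = 0.5, 1 and 2.

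**4. FCC attendance, illustration only.** Take an exponential wait with mean w, post follow-up uniform on 0 to T, and baseline follow-up uniform on 12 to 36 months. The baseline range is inferred from the July 2017 start, the June 2018 registration, and collection not having begun.
- Captured post = 1 − (w/T)(1 − e^(−T/w)).
- Captured at baseline = 1 − (w/24)(e^(−12/w) − e^(−36/w)).
- w = 3: baseline 0.998; post 0.683 (T = 9) or 0.801 (T = 15); post/pre ratio 0.69 or 0.80.
- w = 6: baseline 0.967; post 0.482 or 0.633; ratio 0.50 or 0.66.

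The direction is certain wherever baseline follow-up is longer. The size depends on waits that the article does not give. Referral of high-risk patients is affected in the same direction; its size was not calculated.

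**The case against.** **The 9 months may be a follow-up tail.** Clinical data collection speaks of patient data during implementation and of outcome data for up to 9 months afterwards. If nobody resected in those 9 months is counted, primary truncation is nil. This reading is possible, but the text does not settle it, and the eligibility sentence contains no such limit.

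**The missing-data rule does not mention open windows.** True. But it makes no exception for them either, and a database extract would not separate the two.

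**Cut-offs and outcome windows often belong in an analysis plan.** Also true, and one may exist. The point here is that the article states an eligibility rule that, followed as written, admits patients who cannot be fully observed, and it fixes a window for one outcome but not for the others.

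**Stronger readings that the article does not support**
- *The two periods are not comparable on the primary outcome.* The same 2-month window applies to both, only the end of the post period is affected, and the bias is bounded.
- *The July 2017 anchor lets secular change pass as an intervention effect.* Calendar time in 3-month intervals is a candidate covariate (though selection may drop it), and change common to both concurrent randomised arms does not bias their comparison.
- *Roll-out patients cannot be distinguished.* Time since implementation, also a candidate covariate, can separate them.
- *Baseline should be moved to end when phase 2 starts.* The baseline audit is phase 1, so the latest baseline patients would then lack their own 2-month window.

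**Conclusion.** The concern holds in a limited form. On the literal eligibility rule, up to 22% of post patients (13% if roll-out counts as post) lack the full primary window, and the primary pre/post ratio is pulled towards or below 1. With mean completion at 1 month the factor is 0.89 or 0.93 at worst; over the assumed range of completion times it runs from 0.78 to 0.97. Truncation largely cancels between arms if post periods are equal, but a limit of up to 9 months does not ensure that they are.

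For high-risk referral and FCC attendance, unequal follow-up biases the pre/post comparison downward by an amount that cannot be determined from the article. The attendance ratios of 0.50 to 0.80 illustrate assumed waits and are not estimates for this trial.

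Even resection dates, completion times, waits and the length of baseline follow-up are all assumptions. The existence and direction of the bias depend only on the literal eligibility rule, the missing-data rule and longer follow-up at baseline.

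**What to change.** - State a last eligible resection date at least 2 months before final outcome extraction, or keep the resection dates and extract outcomes 2 months later.
- Give high-risk referral and FCC attendance the same fixed window, from resection or from referral, in both periods.
- Count for each outcome only patients whose full window has been observed.
- Use the same post-period length in all networks.

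With the cut-off or the later extraction, every included patient has the full primary window and the truncation factor becomes 1.00.

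**Cost.** Ending eligibility earlier removes about 133–333 post patients, leaving 467–1,167 (7 months) or 867–2,167 (13 months). The loss is greater if the attendance window is longer than 2 months. Extracting 2 months later costs time but no patients for the primary outcome. As collection had not begun when the article was written, the change is to wording and extraction dates.

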### Perceived barriers

#### Questionnaire

The validated IPSBQ [37] will be used to assess barriers to the relevant target behaviour for change in relation to LS identification and referral, incorporating additional items to reflect the 14-domain TDF developed by Cane et al. (2012) [19]. Participants in the theory-based implementation arm will be provided with results from the IPSBQ to facilitate barrier identification and development of targeted intervention strategies as part of the implementation process. Participants in the non-theory trial arm will also complete the IPSBQ, but only for the purpose of measuring changes in perceived barriers pre-post intervention.

#### Theory-based focus group schedule

The content of the theory-based focus group schedules and additional materials (see Additional file 2) was developed based on the TDFI to encourage discussion of barriers explicitly in the context of the TDF [16, 38].

#### Non-theory based focus group schedule

The content of the non-theory based focus groups and additional materials (see Additional file 2) was developed to promote generic discussion of barriers based on intuition and tacit knowledge, and does not include IPSBQ results or TDF-guided questions about barriers and interventions [38].

### Procedure (detailed description of implementation intervention)

The Implementation Lead at each site will oversee the 7 study phases described below. Phases 4 and 5 will differentiate the theory-based and non-theory based components of the implementation approaches, according to trial arm allocation; the non-theory based components have been modified from the TDFI approach [16]. Phases 1–3 and 6–7 will remain the same for both arms. The study procedures for enrolment, intervention procedures and assessment are presented in the SPIRIT diagram in Fig. 2.

**Fig. 2 Fig2:**
[figure not shown]
Standard Protocol Items: Recommendation for Interventional Trials (SPIRIT) diagram. Schedule for enrolment, intervention procedures and assessment. IPSBQ, Influences on Patient Safety Behaviours Questionnaire

#### Implementation Lead training and ongoing support

The standard training content received by both groups was developed based on common components of comprehensive implementation initiatives utilised by health services for the purposes of improvement [16, 39]. Differences in training materials used in the trial arms will be distinguished only by the inclusion of additional TDF-guided content in the theory-based implementation arm. The training will comprise an introduction to implementation science and specific instructions, practical activities and tools for moving through the 7 phases of the implementation approaches described below (see Additional file 2 for description of training contents). Implementation Leads will be informed of planned teleconference calls with the research team over the study period to support the delivery of each phase, and provided with additional tools for recording study-related activities for process evaluation purposes. These teleconferences will be used to identify and address challenges to participant recruitment and to record and manage any unintended effects of the interventions. Site-specific data management plans, including measures to protect confidentiality of individual participants, will be communicated to Implementation Leads during teleconferences.

#### Phase 1 - undertake baseline audit

The Implementation Leads at each site will undertake data extraction using the clinical practice data extraction tool to establish baseline evidence on existing LS referral practices (see Additional file 2 for data variables). These data will be de-identified and securely transported to the research team. The research team will carry out data checks and undertake site specific analyses for the purpose of presenting local results back to each site.

#### Phase 2 - form the Implementation Team

At each site, key LS patient pathway stakeholders will be identified by the Implementation Lead and invited to form an Implementation Team of 8–10 multidisciplinary change agents [16, 21, 40]. This will consist of healthcare professionals and administrators working in departments involved in the LS identification and referral pathway (including, but not limited to genetic counsellors, colorectal surgeons, pathologists, oncologists, nurses, administrative staff, multidisciplinary team (MDT) meeting coordinators). These individuals will bring expertise from various roles and departments, and therefore increase the likelihood of implementation success [41]. The Implementation Team (led by the Implementation Lead and with support from the research team) will work together through each phase and will also assist in recruiting other LS patient pathway stakeholders to relevant study activities.

#### Phase 3 - identify target behaviours for change

At each site, the Implementation Lead and Implementation Team will participate in two meetings to identify site-specific target behaviours for change. Meeting one will involve a discussion of LS referral pathways, where participants will discuss what they believe current processes and practice to be. Based on these discussions, the Implementation Lead will generate a LS referral pathway process map, which will be later refined in collaboration with the research team. These site-specific process maps will allow the research team to identify key aspects of the process to improve and any key hospital differences.

Prior to meeting two, baseline clinical data (extracted in phase 1 and analysed by the research team) will be mapped to relevant components of the referral process. During the meeting, Implementation Team members will reflect on their experiences of and beliefs about the referral process in light of the baseline clinical data, and explore possible system and/or behavioural change targets. Identifying the target for behaviour change will involve consideration of the impact of changing the behaviour on the desired outcome; whether the behaviour change is achievable; the likely impact (positive or negative) on other, related behaviours and the degree to which the behaviour can be measured [42]. The Implementation Lead and research team will use this information to confirm the target behaviour(s) for change.

#### Phase 4 - identify and confirm barriers to change

LS patient pathway stakeholders in both arms will complete the IPSBQ [37], and be invited to participate in a focus group. Focus groups will be facilitated (by the Implementation Lead) according to a theory-based or non-theory based format, depending on trial arm allocation (see Additional file 2 for focus group schedules). A member of the research team (NT) will attend meetings via video link to support discussions and elicit more in-depth responses.

##### Theory-based implementation arm

Focus group participants will be made aware that the IPSBQ assesses barriers according to theoretical domains explicitly linked to the identification of behaviours. They will be presented with the IPSBQ results from their site, discuss barriers in the context of the TDF and come to a consensus about the top 3–4 barriers overall. The research team will undertake a theory-based analysis of the focus group data to generate an initial implementation package, based on identification of intervention strategies informed by behaviour change techniques (BCTs) matched to identified barriers. This package will be discussed and refined by the Implementation Lead and the research team.

##### Non-theory based implementation arm

In contrast to the theory-based arm, participants will have completed the questionnaire for the purposes of measuring perceptions of barriers pre-post intervention, but will not be shown the results. Focus group participants will be asked to consider the confirmed target behaviour and develop intervention strategies based on intuition and tacit knowledge. Members of the research team (without expertise in coding and operationalising the TDF and BCTs but with expertise in implementation) will undertake a non-theory based analysis of the focus group data to generate an initial implementation package, based on identification of intuitive intervention strategies to address intuitively identified barriers. This package will be discussed and refined by the Implementation Lead and the research team.

#### Phase 5 - generate intervention strategies

For both arms, the Implementation Lead will invite LS patient pathway stakeholders to participate in a second focus group to identify and confirm intervention strategies. As in phase 4, focus groups will be facilitated differently according to trial arm allocation (see Additional file 2 for focus group schedules). Detailed descriptions of the intervention strategies used to address key barriers will be reported in accordance with Standards for Reporting Implementation Studies (StaRI) guidelines [43].

##### Theory-based implementation arm

Focus group participants will be presented with a table of barriers mapped to the TDF and solutions mapped to BCTs.

